#### 2.8.3 Analysis Plan for Secondary Objectives

The number and percent of adverse events within each treatment arm will be reported by grade. We will compare changes between the arms in insomnia, anxiety, depression, fatigue, quality of life, and pain medication usage scores using linear regressions predicting these endpoint scores at Day 7 and Day 14 (separate models) as a function of treatment arm, controlling for baseline score and randomization strata. This is equivalent to an ANCOVA model. The same analysis will be performed for PPT for the baseline (45 min after patch application) and Day 7 assessments, controlling for the pre-patch baseline assessment. We will summarize responses to the PGIC at days 2, 7, and 14 using frequencies and percentages by arm, and test for differences between arms using chi-square tests. To obtain estimates of the correlation of treatment expectancy and treatment response, we will fit a LMM similar to that specified for the primary objective, but with the addition of METE score and the interaction between treatment arm and METE score. To evaluate whether PPT predicts treatment response, we will fit a LMM similar to that specified for the primary objective, but with the addition of baseline (pre-patch) PPT score and the interaction between treatment arm and PPT baseline (pre-patch) score. Pain response variations in associated with other variables, such as sex, race/ethnicity, or age, may be addressed in post hoc analyses.

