
### 2.7 Sample Size Estimation

The main objective of this study is to provide preliminary data on the effect of PRP in reducing musculoskeletal pain compared to placebo plaster. We conservatively anticipate lost to follow up to be at most 10% by day 7. To ensure adequate power to compare arms on our secondary symptom endpoints, we will enroll 66 patients to obtain at least 60 patients evaluable for these secondary symptom endpoints. Our sample size will provide sufficient statistical power to detect clinically relevant effect sizes for our primary pain outcome between PRP vs. placebo plaster (primary objective). We present our power considerations for an ANCOVA regression model (e.g., predicting Day 7 pain score controlling for baseline pain score), which we will apply to our primary pain endpoint as well as to the secondary symptom endpoints. However, our analysis method for our primary endpoint (linear mixed model) will be able to detect a slightly smaller effect size than presented here. For our sample size/power considerations, we calculated the smallest standardized effect size we will be able to detect with 0.80 power, given a sample size of 60. With 30 participants in each of the two arms, we will have power of 0.80 to detect an effect size of 0.74 (standardized mean difference, Cohen’s d) between the two arms at Day 7, using a two-sided test with alpha of 0.05 in a regression model controlling for baseline score. This 0.74 effect size is considered a moderate-to-large effect size by convention. Given the standard deviation of the BPI pain severity subscale typically ranges between 2 and 3, this effect size translates to a mean difference between the arms of around 1.5 to 2.25 points on the 0–10 BPI scale. A 1-point difference in BPI severity is clinically important (Dworkin et al., 2008). In addition, this criteria is also used in a recent high-impact publication comparing opioid vs. nonopioid medication for chronic low back pain (Krebs et al., 2018). Even if we find no statistically significant difference between the arms on the primary endpoint, we will estimate and report the observed effect size and 95% confidence interval to assist in planning potential larger trials.

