#### 2.8.1 Populations for Analyses

All randomized patients will have a baseline pain assessment, and those with at least one post-baseline BPI assessment on or before Day 7 will be included in the analysis of the primary objective using the modified ITT principle (i.e. participants will be analyzed according to the treatment group to which they will be randomly allocated regardless of treatment adherence status). Secondary outcome such as insomnia, anxiety, depression, fatigue, and quality of life are measured at baseline, Day 7, and Day 14. The analysis population for these endpoints will include patients who complete the baseline and one or both of the Day 7 and Day 14 assessments. Pressure pain threshold is measured at baseline before patch application, baseline 45 min after patch application and Day 7. The analysis population for this endpoint will include patients who complete the test at baseline before patch application and one or both of the other two timepoints. Additionally, all patients who apply at least 1 of the study plasters will be included in the analysis of safety.

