#### 2.8.2 Analysis Plan for Primary Objective

We will plot the outcome measure trajectories by randomization arm over time and summarize each outcome measure at each assessment time by treatment arm using descriptive statistics. We expect patients’ pain levels to decrease upon first application of the PRP and then stay at a similarly decreased level with continued use over the study period. Accordingly, we will test for differences between the two study arms in post-Baseline BPI severity using a linear mixed model (LMM) predicting post-Baseline BPI severity as a function of treatment arm, controlling for Baseline BPI severity, assessment time, and randomization strata (baseline opioid use, yes/no). The test of differences between randomization arms with respect to the outcome will be based on the coefficient for treatment arm in this LMM. For our test of differences between the arms in the primary endpoint (Day 2–7 BPI severity), the LMM will have BPI severity assessments through Day 7. We will fit a similar model with BPI assessments through Day 14, but the Day 7 model will be our primary test of efficacy.

To enhance patient-centered data interpretation and decision-making, we will also perform responder analyses by considering those who experienced 30% or greater reduction in BPI severity as responders at the primary end point/Day 7 and at the end of treatment/Day 14.(Farrar et al., 2000; Farrar et al., 2001; Farrar et al., 2010). We will compare the proportion of responders in PRP and placebo plaster groups at both time points using descriptive cross-tabulations and logistic regression adjusting for the baseline outcomes and randomization strata.

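### Separate Day 7 and Day 14 regressions for the secondary scales each use only part of the stated population and leave the later contrast open to a small dropout bias

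*Protocol article*

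**What the plan says.** Section 2.8.3 compares the arms on the secondary symptom, quality-of-life and pain-medication scores with "linear regressions predicting these endpoint scores at Day 7 and Day 14 (separate models) as a function of treatment arm". Each model is adjusted for the patient's starting value and the opioid stratum. The section adds: "This is equivalent to an ANCOVA model". For PPT it states: "The same analysis will be performed for PPT for the baseline (45 min after patch application) and Day 7 assessments".

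Section 2.8.1 sets the population for the symptom and quality-of-life scales as "patients who complete the baseline and one or both of the Day 7 and Day 14 assessments", and for PPT as "patients who complete the test at baseline before patch application and one or both of the other two timepoints".

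The primary outcome is handled differently. Section 2.8.2 tests it "using a linear mixed model (LMM) predicting post-Baseline BPI severity as a function of treatment arm", with repeated assessments through Day 7.

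On loss, section 2.7 says only this: "We conservatively anticipate lost to follow up to be at most 10% by day 7". It gives no figure for Day 14. The sample size was set with these scales in mind: "we will enroll 66 patients to obtain at least 60 patients evaluable for these secondary symptom endpoints".

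The article describes no imputation or joint model for the secondary scales.

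**The concern.** A rule that admits patients with either visit is what a repeated-measures model needs. A regression on a single visit cannot apply it, because it drops everyone without that visit. A patient with Day 7 but no Day 14 belongs to the stated population, yet contributes nothing to the Day 14 estimate. The Day 14 model also ignores the Day 7 score, which is the most recent information on who left and how they were doing.

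At stake is the later contrast. Suppose placebo patients with poor Day 7 scores leave more often, while losses on the active plaster are unrelated to the score. The placebo patients who remain then look too well at Day 14, and the arm difference shrinks. Estimating change in these symptoms is the second aim in the Introduction, and the trial is meant to inform a larger one, so a distorted estimate could carry forward.

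**Working it through.** **1. The plan's own figure.** Inputs from section 2.7: 30 per arm, two-sided alpha 0.05, d = 0.74. The noncentrality is 0.74/√(1/30 + 1/30) = 0.74/0.258 = 2.87. With 57 degrees of freedom the power is 0.804, and the exact detectable d at 0.80 power is 0.736. For enrolment, 66 × 0.90 = 59.4, about 60. The stated sample size reproduces and is not in dispute.

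**2. Who enters which model** (symptom scales, baseline present):

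| Visits completed | In the 2.8.1 population | In the Day 7 model | In the Day 14 model |
|---|---|---|---|
| Both | yes | yes | yes |
| Day 7 only | yes | yes | no |
| Day 14 only | yes | no | yes |
| Neither | no | no | no |

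The two models together reach everyone in the population. Neither does alone.

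**3. When a single-visit model is biased.** It is valid if loss depends only on arm, baseline score and stratum. It can fail if loss after Day 7 depends on the Day 7 score differently by arm.

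**4. Size with no true effect.** Assumptions, none of them in the documents: 33 per arm, all seen at Day 7; baseline, Day 7 and Day 14 scores with SD 1 and common correlation ρ; logit P(Day 14 missing) = logit(p) + s × Day 7 score; 4,000 trials per setting.

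- Separate estimate: the arm coefficient from regressing Day 14 on arm and baseline among those seen at Day 14.
- Joint (likelihood) estimate: γ_arm + γ_7 × β_arm. The γ come from Day 14 on arm, baseline and Day 7 in completers. β_arm comes from Day 7 on arm and baseline in all patients.

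Bias in SD for p = 0.05 / 0.10 / 0.15 / 0.20:

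| Loss pattern | Separate, ρ = 0.5 | Separate, ρ = 0.7 | Joint, range |
|---|---|---|---|
| Random (s = 0) | 0.001 / 0.004 / 0.004 / −0.001 | −0.002 / −0.002 / −0.001 / 0.000 | −0.002 to 0.004 |
| Same in both arms (s = 1) | 0.004 / −0.003 / 0.000 / 0.000 | 0.003 / 0.002 / −0.003 / 0.003 | −0.003 to 0.004 |
| Placebo only (s = 1; active 0) | 0.018 / 0.026 / 0.046 / 0.051 | 0.014 / 0.028 / 0.038 / 0.047 | −0.005 to 0.004 |
| Opposite (s = 1; active −1) | 0.037 / 0.061 / 0.081 / 0.107 | 0.034 / 0.056 / 0.071 / 0.092 | −0.003 to 0.006 |

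The standard error is about 0.18–0.25 SD and nearly the same for both methods. Simulation error is about 0.25/√4000 = 0.004. The second row holds for no true effect. With a true effect the Day 7 scores differ between arms, so equal dependence would not be exactly neutral.

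**5. Size with a true effect of 0.5 SD.** Assumptions: baseline correlation 0.5, Day 7–Day 14 correlation 0.7, 10% lost after Day 7, active-arm loss random, placebo loss driven by the Day 7 score. Large-sample Day 14 ANCOVA, by rise in the odds of loss per SD of Day 7 score:

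| Odds ratio per SD | Estimate | Shortfall |
|---|---|---|
| 1.5 | 0.48 | 0.02 |
| 2 | 0.47 | 0.03 |
| 3 | 0.45 | 0.05 |
| about 10 | 0.43 | 0.07 |
| worst 10% of placebo removed | 0.41 | 0.09 |

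With 33 per arm and slopes of 1 to 2, the separate model gave 0.46 to 0.44 and the joint estimate 0.50. Loss in opposite directions gave 0.42 against 0.50.

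**6. Precision.** Under random loss of 10% and 15% in the step 5 setting, the ratio of joint to separate variance was 0.968 and 0.947, a gain of 3% and 5%. In standard error this is 1 − √0.968 = 1.6% and 1 − √0.947 = 2.7%.

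**7. PPT.** It was not simulated separately, but the structure is the same, with 45 minutes as the earlier reading and Day 7 as the later one. The planned ceiling of 10% loss by Day 7 applies directly here (66 × 0.10 = 6.6 patients). Whether that loss depends on the 45-minute reading is an assumption.

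**The case against.** The other side has a good case, and most of it stands.

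- A reader might infer that the two sections contradict each other, or that the plan cannot analyse its stated population. The documents do not support that. Section 2.8.1 does not say that every model contains every patient, and the pair of models reaches everyone.
- ANCOVA by visit is standard. Section 2.7 bases power on it and says it will be applied to these endpoints, so it is a deliberate and consistent choice. An analysis plan that is not shown could add imputation.
- A reader might infer that every visit is exposed. If patients who leave do not return, everyone seen at Day 14 was also seen at Day 7, and a joint model adds almost nothing to the Day 7 symptom contrasts. Patients lost before any post-baseline visit are not recovered either, and the only loss that the article quantifies for the symptom scales is loss by Day 7.
- A reader might infer that the Day 14 effects will be about 14% too small (0.07/0.50). That needs roughly a ten-fold rise in the odds of loss per SD, in one arm only. Nothing in the article supports loss of that kind in a blinded 14-day trial.

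One part is not answered. As written, the later contrast discards an earlier score that has been collected and bears on who left. A joint model gives the same answer when data are complete and protects against this pattern of loss. That makes it more than a matter of taste.

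**Conclusion.** The point holds in a limited form. Each planned regression uses only the patients seen at its own visit and ignores the other post-baseline score. The exposed estimates are the Day 14 symptom contrasts and the Day 7 PPT contrast, and only if later loss depends on the earlier score differently by arm.

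Under the assumed 5–20% later loss and correlations of 0.5–0.7, the bias is about 0 for random or arm-equal loss, about 0.01–0.07 SD for dependence in one arm, and up to about 0.1 SD in extreme cases. Against a standard error near 0.2 SD, even the largest simulated value is under half a standard error (0.107/0.245 = 0.44). On the PROMIS T-score, if the trial's SD matches the reference value of 10, 0.07 SD is 0.7 points. The precision gain from a joint model is only about 3–5% in variance.

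A reader might also infer a threat to the primary result. There is none: the primary outcome already has its own mixed model. Severity is low.

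**What to change.** In section 2.8.3, replace the two regressions per scale with one linear mixed model that takes both post-baseline visits as repeated outcomes:

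- unstructured covariance between the two visits;
- arm, visit, arm-by-visit, baseline score, baseline-by-visit and opioid stratum, plus stratum-by-visit if exact agreement with the per-visit ANCOVA on complete data is wanted;
- the arm contrast reported at each visit.

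Do the same for PPT with the 45-minute and Day 7 readings and the pre-patch value as baseline. This model uses the population that section 2.8.1 already defines. Keep the per-visit ANCOVA as a sensitivity analysis. If the separate regressions are kept as the main analysis, section 2.8.1 should at least define the population visit by visit.

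The cost is analysis wording and slightly more modelling work. It needs no new data and no change to the sample size, and the trial already fits mixed models. The downside is reliance on a missing-at-random assumption, which should be stated.

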### 2.3 Randomization and Allocation Concealment

Participants will be randomized in a 1:1 ratio to the PRP or placebo plaster groups using MSK’s Clinical Research Database (CRDB), a secure computer system that ensures full allocation concealment. Permuted block randomization methods with stratification by baseline opioid use (yes/no) will be utilized. Participants’ treatment assignments can be viewed in the CRDB only by the hospital pharmacists who are dispensing the study medication.

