#### 2.6.2 Secondary Outcomes

• Pain severity and interference measured by the BPI at day 14.• Patients’ Global Impression of Change (PGIC) is a one item survey that will be used to define a clinically important change in pain from the patient’s perspective (Sloan et al., 2002). Patients will be asked “Compared to when the study began, how would you describe your pain now? I am: very much worse, much worse, a little worse, the same, a little improved, much improved, very much improved.” The PGIC can be used as an anchor to derive anchor-based minimally important differences (MIDs) for pain measures like the BPI.• Brief Fatigue Inventory (BFI) will be used to determine the effect of treatments on fatigue. This 9-item instrument was designed to assess one construct of fatigue severity in cancer and non-cancer populations. Three items ask patients to rate the severity of their fatigue at its “worst,” “usual,” and “now” during normal waking hours, with 0 being “no fatigue” and 10 being “fatigue as bad as you can imagine.” Six items assess the amount that fatigue has interfered with different aspects of the patient’s life during the past 24 h. The interference items are measured on a 0–10 scale, with 0 being “does not interfere” and 10 being “completely interferes” (Sloan et al., 2002). A composite fatigue severity score can be found by averaging the nine item scores. The score of the scale was found to be reliable and valid in multiple languages and diverse populations (Sloan et al., 2002; Lin et al., 2006).• Insomnia Severity Index (ISI) will be used to measure subjective insomnia severity. The ISI has seven items rated on a 5-point Likert response scale (e.g., 0 = no problem; 4 = very severe problem), yielding a total score ranging from 0 to 28 with higher scores representing more severe insomnia symptoms. The usual recall period is the “last month”; however, we will use a modified recall period of “the past week” to match our assessment schedule. The ISI authors suggest the following guidelines for interpreting the ISI total score: < 8, no clinically significant insomnia; 8-14, subthreshold insomnia; 15-21, clinical insomnia (moderate severity); >21, clinical insomnia (severe).(Bastien et al., 2001). The ISI has demonstrated internal consistency, reliability, construct validity, specificity and sensitivity in a representative sample of 1670 cancer patients.(Savard et al., 2005). The ISI has established minimally important change values to ensure that the change is not only statistically, but also clinically, meaningful to patients.(Morin et al., 2011). A reduction of eight points has been deemed to be clinically significant improvement. (Morin et al., 2011).• Hospital Anxiety and Depression Scale (HADS) will be used to explore the effect of treatments on psychological distress. HADS is a 14-item scale with seven items measuring depression and seven items measuring anxiety. Each item is answered by the patient on a four-point (0–3) response category so possible scores range from 0-21 for anxiety and depression, with higher scores indicating higher symptomatology. Established cutoffs are: 0–7 not significant; 8–10 subclinical; and 11–21 clinically significant depression/anxiety.(Zigmond and Snaith 1983). Factor analysis showed two distinct but correlated factors of anxiety and depression.(Moorey et al., 1991). The scale scores have been shown to be both reliable and valid.(Smith et al., 2002).• Patient Reported Outcomes Measurement Information System (PROMIS®) Scale v1.2 - Global Health is a brief instrument composed of 10 items that demonstrates adequate reliability and validity (Hays et al., 2009; Revicki et al., 2009) as a measure of health related QOL in general and clinical populations.(Rothrock et al., 2010; Barile et al., 2013). Patients are asked to respond to questions 1-8 and 10 on a scale of 1–5. Question nine is on a 0–10 scale (average pain rating). The measure yields two scores, Physical Health and Mental Health, that will be used as secondary outcomes to evaluate the effect of Tibetree PRP on QOL.(Hays et al., 2009). These scores will be calculated using item-level calibrations based on item response theory (IRT) scaling and then transformed to T-Scores, which are standardized such that 50 represents the mean for the US general population, and the standard deviation around that mean is 10 points.(Hays et al., 2009). Higher scores indicate better Physical and Mental Health.• MAO Expectancy of Treatment Effects (METE) has four items originally developed as the Acupuncture Expectancy Scale (AES) by Mao et al.(Mao et al., 2007) It has demonstrated reliability (Cronbach’s α of 0.82) and validity and is positively correlated with patient self-reported efficacy and satisfaction.(Mao et al., 2007). The score ranges from 4 to 20, with higher scores indicating greater expectancy.• Mao Expectancy of Side Effects of Treatment (MESET) measures the expectations of side effects and therapeutic effects of the study intervention.(Mao et al., 2014). The score ranges from 4 to 20, with higher scores indicating greater expectancy for side effects. We will use the METE and MESET to explore whether expectancy predicts treatment outcomes and may impact the observed differences between groups.• Pressure Pain Threshold: This is a study measure that a study investigator will administer. Pressure algometry is a reliable measure of pressure pain threshold. Two types of algometers will be used in this trial:(1) the FPX Wagner algometer: We will use a digital pressure algometer, FPX (Wagner instrument, Greenwich, United States), to apply pressure at the site of pain (the tender points of tissue where the patient experiences the worst pain) and two pain-neutral areas (thumbnail bed and trapezius) to derive the pressure pain threshold (the first pressure that is perceived as painful) shown to be predictive of analgesic effects (Harte et al., 2013a; Wasserman et al., 2015). The clinical researcher will apply pressure at a 0.5 kgf/cm^2^/sec increment at the tissue located at or surrounding the tested site with the tip of the algometer. The test will be terminated when participants reach their pain threshold or a pressure of 10 kgf/cm^2^. The test will be repeated three times per site, and we will take the mean threshold for analysis, measured as kgf/cm^2^. The test will be conducted three times during the study: before patch application at baseline; 45 min after patch application at baseline and at the primary endpoint (Day 7).(2) the MAST system: We will use the MAST System (Arbor Medical Innovations, Ann Arbor, MI) (Harte et al., 2013b; Schrepf et al., 2015; Wasserman et al., 2015; Treister et al., 2018; Harte et al., 2019) to apply computer-controlled pressure at the thumbnail bed to derive the PPT as well as suprathreshold measures of pain sensitivity (e.g., pain tolerance) shown to be predictive of analgesic effects.(Harte et al., 2013a; Wasserman et al., 2015). The system delivers ascending and random patterns of discrete pressures (5 s duration; 4 kgf/cm^2^/s ramp rate) at 20 s intervals, beginning at 0.25 kgf/cm^2^ and increasing in 0.25–0.50 kgf/cm^2^ steps. Pain intensity will be rated after each stimulus on a 0–100 Numerical Rating Scale. The test will be terminated when participants reach their tolerance or 10 kgf/cm^2^. PPT test with the MAST system will be conducted once before patch application at baseline only. The validity of testing pressure pain threshold with the MAST system has been demonstrated extensively (Petzke et al., 2001; Gracely et al., 2002; Giesecke et al., 2003; Petzke et al., 2003; Petzke et al., 2005; Harris et al., 2006; Geisser et al., 2008; Harris et al., 2008; Harris et al., 2009; As-Sanie et al., 2013; Henry et al., 2014; Clauw 2015). We will use this measure to explore whether pressure pain threshold predicts treatment outcomes and impacts the observed differences between groups. We will also incorporate the pressure pain threshold into the clinical outcomes to provide more objective, less biased quantification of pain and more accurate assessment of the analgesic effect of the herbal patches.• Study Allocation Belief: This is a patient-reported outcome that asks patient to guess which treatment they have received during the study to assess the adequacy of blinding.• Pain Medication Diary: Name of pain medication, the dosage/strength, number of days patients took the medication and how many pills were taken were collected in the Pain Medication Diary. A pain medication usage score was calculated according to the method developed by Robinson-Papp et al. (Robinson-Papp et al., 2015).• Adverse events: We will document all related adverse events and report any related serious adverse event promptly to IRB.

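### PGIC, a seven-level ordered scale, is compared between arms by chi-square tests that ignore the ordering and the opioid stratum and lose power with about 30 patients per arm

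*Protocol article*

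**What the plan says.** Section 2.6.2 defines PGIC as a single item with seven responses in order: "very much worse, much worse, a little worse, the same, a little improved, much improved, very much improved". It says the item "will be used to define a clinically important change in pain from the patient’s perspective".

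The analysis is in section 2.8.3: "We will summarize responses to the PGIC at days 2, 7, and 14 using frequencies and percentages by arm", and then "test for differences between arms using chi-square tests". The text mentions no collapsing of categories, trend version, exact test, ordinal model or adjustment for the randomization stratum.

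On size, section 2.7 states "we will enroll 66 patients to obtain at least 60 patients evaluable for these secondary symptom endpoints". Its power statement is "With 30 participants in each of the two arms, we will have power of 0.80 to detect an effect size of 0.74", "using a two-sided test with alpha of 0.05 in a regression model controlling for baseline score". It gives no power figure for PGIC.

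The other between-arm efficacy models do adjust for baseline opioid use. These are the linear mixed model for BPI severity and the responder logistic regression (section 2.8.2), and the linear regressions for the secondary scores and pressure pain threshold (section 2.8.3).

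**The concern.** A Pearson chi-square on an arm-by-category table gives the same result however the categories are shuffled. It asks whether the two response patterns differ in any way, and spends up to 6 degrees of freedom doing so. The question for PGIC is directional: did patients on the active plaster report more improvement? A test that uses the order puts its power on that question.

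With about 60 patients, the seven levels also leave thin cells. The test yields a p-value but no effect estimate. Yet the Introduction lists global impression of change among the outcomes for which the trial wants estimates. At stake is a real shift in patients' overall rating that goes undetected, and a secondary result of little use for planning a later trial.

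**Working it through.** **Inputs.** Seven ordered levels (section 2.6.2). Chi-square test, taken as Pearson on all seven levels (section 2.8.3). 30 per arm and two-sided alpha 0.05 (section 2.7). Allocation: "Participants will be randomized in a 1:1 ratio to the PRP or placebo plaster groups" (section 2.3). The article gives no PGIC distribution, so those below are assumptions.

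**1. The plan's own power figure.** For 30 per arm and d = 0.74, the noncentrality is 0.74 x sqrt(30/2) = 2.87. The two-sample t-test then has power 0.805, and the smallest detectable d at 0.80 power is 0.736. The stated 0.80 is reproduced. It covers the regression models, not PGIC.

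**2. Cell counts.** 2 arms x 7 levels = 14 cells. The mean expected count is 60/14 = 4.3, or 66/14 = 4.7 with no dropout. If all seven levels are used, not every expected count can reach 5.

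**3. Degrees of freedom alone.** A 1-df test with power 0.80 has noncentrality (1.960 + 0.842)^2 = 7.85. The same noncentrality on 6 df gives power 0.52. A 1-df test with power 0.50 (noncentrality 1.960^2 = 3.84) falls to 0.26.

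**4. Simulation.** 20,000 trials per scenario, 30 per arm. Pearson chi-square on the observed levels was compared with the tie-corrected Wilcoxon rank-sum test, which is close to the proportional-odds score test. Four placebo distributions were assumed (percent, worst to best):
- 3/7/12/28/27/16/7
- 1/3/8/38/32/13/5
- equal sevenths
- 2/4/10/24/30/20/10

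The active arm was shifted by a common odds ratio (OR) or by a latent normal difference d. Ranges are across the four distributions.

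| Effect | Chi-square, 7 levels | Rank-sum | Power ratio |
|---|---|---|---|
| None (type I error) | 3.0-4.3% | 4.7-5.1% | - |
| OR 2 | 12-15% | 31-32% | 0.39-0.46 |
| OR 3 | 31-34% | 64-66% | 0.48-0.52 |
| OR 5 | 67-69% | 92-93% | 0.73-0.75 |
| d = 0.5 | 18-20% | 44-45% | 0.39-0.46 |
| d = 0.74 | 42-44% | 76% | 0.55-0.58 |
| d = 1.0 | 73-75% | 95% | 0.77-0.78 |

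Across scenarios, 44-69% of cells had an expected count below 5. The customary limit of 20% such cells was exceeded in 89-100% of trials.

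A separate simulation with placebo distribution 1/3/8/38/30/15/5 agreed. Chi-square vs rank-sum power was 33% vs 64% at OR 3, 43% vs 76% at d = 0.74 and 75% vs 95% at d = 1.0, with type I error 3.2% vs 5.2%.

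**5. If categories were collapsed.** A split at much improved or better, tested by an unadjusted two-proportion comparison, had 57-61% power at d = 0.74. That lies between the seven-level chi-square (42-44%) and the rank test (76%).

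**The case against.** The strongest reply is that the article never says the table is 2 x 7. It gives neither the number of categories tested nor the degrees of freedom. Using PGIC to define clinically important change is compatible with an improved/not-improved split, and a collapsing rule or a trend version could sit in an analysis plan that is not shown. Collapsing narrows the gap: with placebo distribution 1/3/8/38/30/15/5 and OR 3, two 2-level splits and one 3-level version had 47-51% power, against 32% uncollapsed and 62% for the rank test. This stands as a limit on the size of the loss. It does not remove the point. The article names a test for a scale it defines with seven levels, all seven is the plainer reading, and even the collapsed versions fall short of an ordinal test.

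A reader might infer more than the documents support:

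- **That power is halved in general.** It is roughly halved only for moderate effects. The relative loss (1 minus the ratio) is 54-61% at d = 0.5, 42-45% at d = 0.74 and 22-23% at d = 1.0.
- **That sparse cells invalidate the test or produce false positives.** The simulated type I error is below 5%. The sparseness makes the test conservative, which is part of the power loss and not a second problem.
- **That PGIC's role as an anchor for the BPI is compromised.** Section 2.6.2 says only that PGIC can serve as an anchor for minimally important differences, and that use does not depend on the between-arm test.
- **That direction would be invisible.** The frequencies and percentages by arm will show it; only the p-value ignores it.

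It is also fair that no quantified harm attaches to omitting the opioid stratum. That part is an inconsistency with the rest of the plan.

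**Conclusion.** The point holds as a worthwhile improvement to a secondary analysis. The stated test suits the scale badly: it discards the order, omits the stratification factor and gives no effect estimate. At d = 0.74, the effect size in the plan's own power statement, it has about 43% power where a rank test has about 76%.

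These figures rest on three assumptions: all seven levels are tested, about 30 patients per arm are evaluable, and the PGIC distributions are as assumed. Applying d = 0.74 to a latent PGIC scale is likewise an assumption, since section 2.7 states it for the regression models. Results changed little across the distributions tried. The primary efficacy test, the Day 7 linear mixed model for BPI severity, is not affected.

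**What to change.** Replace the chi-square wording in section 2.8.3. At Days 2, 7 and 14, compare PGIC between arms with a proportional-odds model containing arm and baseline opioid use, and report the common odds ratio with its 95% CI. This also meets the Introduction's aim of estimating global impression of change. If proportional odds is thought doubtful, prespecify a Wilcoxon test stratified by opioid use (van Elteren). Keep the frequencies and percentages as description. If a collapsed or trend version of chi-square was intended, the text should say so and give the rule.

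The cost is one sentence, with no new data, visits or patients. The small downside is the proportional-odds assumption, which is hard to check with 30 per arm and thin end categories. The stratified rank test needs less but does not itself give an odds ratio.
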